## Abstract

**Background:**

Developing strategies aimed at reducing behavioral risk factors and hence the prevalence of non-communicable diseases (NCDs) is a major challenge to the policy makers today. Like the same age group worldwide, the prevalence of obesity, unhealthy dietary habit, physical inactivity, smoking and alcohol intake is high among the adolescents of Bangladesh. Studies showed promising results of an early intervention at adolescent age in reducing the likelihood of NCDs at adult age. So, this study is designed to implement a behavior change intervention and evaluate the effectiveness of the intervention in reducing the behavioral risk factors of NCDs among the adolescents of Bangladesh.

**Methods:**

A before-after designed intervention study will be conducted in two randomly selected secondary schools- one will be selected randomly as intervention school and the another as control school. A baseline survey will be conducted among the students of both schools by a pre-tested questionnaire to attain their current status of knowledge, attitude and practices related to NCDs. Afterward, students will be enrolled in the intervention group who will meet the eligibility criteria from the intervention school. The intervention will be given through a health promotion session to a group of students, not more than 25 at a time, by trained facilitators. A post-intervention end line survey will be conducted among all the participants from both schools using the same questionnaire 3 months after the baseline survey.

**Discussion:**

An intervention has been developed based on some principals of two psychosocial theory- Motivational Interview and Social Cognitive Theory. Emphasis will be given on motivating the adolescents towards a healthy lifestyle, supporting self-efficacy to be changed, guiding self-regulatory ways along with facilitating desired changing process by empowering them with choices about the preventive measures of NCDs. This intervention is expected to increase awareness by equipping the adolescents with specific knowledge and skills and thus, facilitate an eventual change in their practiced risk behaviors. Besides, this intervention will address multiple behaviors at a time, and will be delivered to a group of adolescents, to attain the cost-effectiveness and thereby making it more realistic in the resource-poor context of Bangladesh.

**Trial registration:**

ClinicalTrials.gov NCT03975335, registered on 01.06.2019. Retrospectively registered.

**Electronic supplementary material:**

The online version of this article (10.1186/s12889-019-7229-8) contains supplementary material, which is available to authorized users.

## Background

Towards addressing the non-communicable diseases (NCDs) epidemic in Bangladesh, effective measures are needed to stifle its emergence. In the case of NCDs, it is useful to start the prevention process at the adolescent stage [1] since most of the behavior related risk factors of NCDs begin to demonstrate at this age [2]. Targeting adolescents also has the additional benefit of reducing the life-time cost of healthcare by addressing the behaviors at the outset [3, 4].

Adolescents of Bangladesh, like the rest of the world, are exposed to significant amount of NCDs risk factors such as obesity [5], less fruit and vegetable intake [6], physical inactivity [7], smoking [8] etc. Given modifiable risk factors are prevalent in large numbers, intervention that aims to change behavior can be an effective method of halting the growth of NCDs. Several theories on how human behavior is shaped have been discussed and evaluated over the past decades or so. For example, attitude towards a behavior and subjective norm or social influence have been emphasized to influence human behavior in many theories including theory of planned behavior [9]. Meta-analysis supported the theory that there is a strong relationship between attitude and behavior, and behavioral intention plays a major role as a mediator between them [10]. Furthermore, greater attitudinal consistency is observed amongst the better informed [11]. Self-efficacy expectation or personal belief to accomplish a change in behavior described by Bandura in his Social Cognitive Theory (SCT) [12, 13] was proven to have successfully predicted behavioral intention [14, 15]. Moreover, adolescents were found in need of tremendous psychological support or motivation to shape positive behaviors [16]. Motivational Interview (MI) postulated by Rollnick & Miller (1995) [17] showed promising results to this effect.

Understanding behavioral risk and protective factors can positively influence the development of intervention programs [18]. Theory-based intervention has proven to be an effective method in driving behavioral change. However, choosing the right intervention technique is a difficult task and needs to be experimented and evaluated in context specific settings [19, 20]. Studies suggested that the choice of a suitable theory base for an intervention should begin with identifying the problem, goal, and units of practice [18]. Also, intervention targeting multiple behavior has been proven to have greater impact than single behavior intervention [21, 22].

Considering all these aspects, an intervention has been designed to reduce NCDs related risk behaviors such as unhealthy dietary habit, physical activity and smoking among the adolescent of Bangladesh considering some of the components of MI and SCT. In this intervention, emphasis is given on evoking adolescents’ internal desire to change, supporting self-efficacy to be changed, guiding self-regulatory ways along with facilitating desired changing process by empowering them with choices and skills. It is to clarify that, this study will not measure the efficacy of the theory of MI or SCT, rather the effectiveness of the proposed intervention will be evaluated which has been constructed based on some principles of the former theories. This intervention is expected to increase awareness by equipping the adolescents with specific knowledge, motivating them, and facilitating an eventual change in their practiced risk behaviors.

## Objectives

### General objective

To design and investigate the efficacy of a health education intervention to reduce NCD related behavioral risk factors among adolescents in institutional settings of Bangladesh.

### Specific objectives

To conduct a baseline survey to evaluate the knowledge, attitude and practices about NCD risk behaviours such as unhealthy diet, physical inactivity, smoking etc. among the respondents.To develop a health education intervention based on the baseline survey to reduce NCDs related behavioural risk factors among adolescents.To apply the health education intervention to the target group through effective communication approach and tools.To conduct a post interventional survey with the same questionnaire used in baseline data collection.To evaluate the intervention by comparing pre and post intervention data.

## Methodology

### Study design and setting

A before-after designed intervention study will be conducted in two randomly selected secondary schools in a semi-urban area of Dhaka, capital of Bangladesh. One school will be selected randomly as intervention school and the other one as control school. Possibility of diffusion of intervention contents among students from one school to another will be minimized by selecting the schools at a reasonable distance.

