### Participant recruitment and data collection

The study will follow a fixed study design (Additional file 1). Sample size is determined based on a previous study where a mean difference of BMI was found 1.48 between intervention and non-intervention adolescent groups after 3-months of motivational interview [23]. Expecting a similar difference, calculated sample size is 274 in each group considering effect size (E) = 1.48; standard deviation (S) = 5.98; standardized effect size (E/S) = .25; significance level, α (two-sided) = 0.05; β = 1- power = 0.2, non-response rate = 5%]. A complete list of grade-ten students will be prepared after collecting their class roll and batch number from the administrative offices of the selected schools. All the students of grade-ten will be invited to participate in the study through announcement and personal contact prior to the date of data collection.

At first, a baseline survey will be conducted among the grade ten students of both schools by a pre-tested questionnaire to attain their current status of knowledge, attitude and practices related to NCDs. Then, students from the intervention school who reported at least two NCDs risk behaviors will be invited to participate in a health education session through phone call to their parents. Selected students who will present at the day of intervention will be considered having implied consent from their parents and will be enrolled in the intervention group up to the attainment of the required sample size. Enrolled students will be given intervention through health education session. Students with any kind of physical disability or limited movement will be excluded from the study. Students from the control group will receive a one-hour session on carrier guidance. Students will be kept blind about the intervention they received. After 3 months of the baseline survey, a post-intervention survey will be conducted among the participants from both intervention and control group using the same questionnaire.

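### With one school per arm and distance the only stated condition linking the two, the random draw can pair dissimilar schools; comparable pairs should be formed before the draw

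*Protocol article*

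**What the plan says.** Study design and setting states: "A before-after designed intervention study will be conducted in two randomly selected secondary schools in a semi-urban area of Dhaka". It continues: "One school will be selected randomly as intervention school and the other one as control school". The spread of intervention content between schools "will be minimized by selecting the schools at a reasonable distance". That section gives no criterion for sex composition, management type, living standard or grade size.

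Participant recruitment and data collection draws everyone from grade ten and gives the target: "calculated sample size is 274 in each group". In the intervention school, students who report at least two risk behaviours and attend on the day "will be enrolled in the intervention group up to the attainment of the required sample size".

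The Statistical analysis plan section tests background characteristics between the groups. It assesses efficacy by paired t and McNemar tests on before-after data, and compares the groups on pre- and post-intervention status. The regressions relate socio-demographic variables to change; they are not described as adjusting the intervention effect. The Discussion expects the students counselled together to be alike in age, sex, socio-economic status and risk behaviour.

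**The concern.** Randomisation balances over many units. With two units it decides only which school receives the intervention; whatever gap exists between the schools becomes a gap between the arms. The selection rule is therefore the main place where comparability can be protected, and the stated rule controls only distance, level of schooling and area.

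At stake is whether a difference between the groups can be read as an effect of the session. A boys' school set against a girls' school, or a fee-charging school against a poorer one, would give a difference that a reader could not attribute. The Discussion's expectation of homogeneity in sex and socio-economic status is not secured by any selection step. Session groups are formed by roll number, and nothing ties the make-up of one school to that of the other.

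**Working it through.** **1. The plan's own figure.** Inputs from Participant recruitment and data collection: "considering effect size (E) = 1.48", "standard deviation (S) = 5.98", two-sided α 0.05, power 0.80, non-response 5%.

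- n per group = 2 × [5.98 × (1.96 + 0.8416) / 1.48]² = 256.3, so 257.
- With 5% non-response: 257 / 0.95 = 270.5, so 271, within 3% of the stated 274.

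The figure is reproduced. It treats students as independent and contains no term for the school.

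**2. Where a school difference enters.** Write each school's post-intervention mean as baseline level + trend over three months + (intervention school only) effect.

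- Post-intervention comparison = effect + (difference in levels) + (difference in trends).
- Comparison of changes = effect + (difference in trends). Stable level differences cancel.
- Paired test within the intervention school = effect + that school's own trend. The control school plays no part.

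If the effect itself differs by sex or living standard, each line estimates the effect for the mix of the drawn intervention school.

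**3. Sex composition as an example.** If the share of boys differs by p between the schools, and boys and girls differ by d on the outcome (or on its change), the contribution is p × d. It is zero for equal mixes, half of d at p = 0.5, and all of d at p = 1. At p = 1 sex and arm coincide and no model can separate them. The document gives neither p nor d.

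**4. Illustration on the sample-size outcome.** The intraclass correlation (ICC) values are assumptions. With 260 analysed per school (274 × 0.95), the standard deviation of the chance gap between two school means is 5.98 × √(2 × ICC). The type I error of a student-level test is 2 × [1 − Φ(1.96 / √(1 + 259 × ICC))].

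| Assumed ICC | SD of gap, BMI units | Type I error |
|---|---|---|
| 0.001 | 0.27 | 8% |
| 0.005 | 0.60 | 20% |
| 0.01 | 0.85 | 30% |
| 0.02 | 1.20 | 43% |

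These figures are for an unadjusted comparison of post-intervention means. In a comparison of changes the stable part of the gap drops out.

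**5. Grade size, as a feasibility check only.** Roll needed in the intervention school = 274 / (eligible share × attendance). On assumed shares:

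- 90% and 90%: 338.3, so 339.
- 80% and 80%: 428.1, so 429.
- 70% and 70%: 559.2, so 560.

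If each group reached only 250, 200 or 150, power for the BMI difference before any loss would be about 79%, 70% or 57%.

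**The case against.** **The main stated analysis is before-after, so level differences cancel.** This stands for the paired tests and for any comparison of changes. It does not cover differing trends or responses, nor the planned comparison of post-intervention status.

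**Random assignment favours neither school.** True over repeated draws, but there is one draw. The gap in that draw stays in the result, and student-level tests do not count it.

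**Measured characteristics can be adjusted for.** Gender, parental education, parental occupation and living standard are recorded for each student. A reader might infer that no school difference could ever be corrected; the document does not support that. Characteristics that overlap between the schools can be adjusted for. Complete separation, as with opposite single-sex schools, and purely school-level attributes cannot.

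**The draw is not unrestricted.** Both schools are secondary, in a semi-urban area, and one grade is studied. Distance is the only stated condition relating the two schools to each other, not the only condition.

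**Details may sit elsewhere.** Additional file 1 is not shown, and a condensed article may omit a sampling frame. That weakens any complaint about a missing minimum roll. It does not change the selection rule that the article states.

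**Grade ten may be too small for 274.** A reader might infer that the target is unreachable. No roll, eligible share or attendance rate is given, and the risk-behaviour definitions are broad, so a low eligible share is not supported. Nor does the 5% fall short here: ineligibility and absence on the session day come before enrolment, and a non-response allowance is not meant to cover them.

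**Matching still leaves one school per arm.** Correct. The protocol cites limited time and funds and commits to reporting guidance for non-randomised designs, so matching is an improvement within the design, not a cure.

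**Conclusion.** The point holds as a weakness in the selection rule. As written, the draw can pair schools that differ in sex composition, management type or living standard. The article states no adjusted effect or difference in change that would offset this. The unadjusted post-intervention comparison is exposed to both level and trend differences; a comparison of changes is exposed to differing trends or responses.

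The size cannot be fixed from the document. On assumed ICCs of 0.001 to 0.02, the standard deviation of the chance gap is 0.27 to 1.20 BMI units, about 18% to 81% of the assumed 1.48 (0.27/1.48 and 1.20/1.48). This shows that a modest school effect matters; it does not estimate one. How likely a badly matched pair is also cannot be stated. Missing 274 is a possibility that depends on rates not given, not a demonstrated shortfall.

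This is a cheap improvement worth making before the schools are drawn. It does not show that the study must fail.

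**What to change.** In Study design and setting, replace the unrestricted draw of two schools with these steps:

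1. List the eligible semi-urban secondary schools with sex composition, management type, area or fee level, and grade-ten roll.
2. As a feasibility check, keep schools whose grade-ten roll can plausibly supply 274 enrolled students, stating the eligibility and attendance rates assumed.
3. Form pairs at the required distance that match on sex composition, management type and area or fee level. Give sex composition priority if few pairs qualify, because its complete separation cannot be repaired in analysis.
4. Draw one pair at random, then assign the arm within it at random.
5. State as a limitation that one school per arm leaves school and intervention confounded even after matching, and that separating them would need more schools per arm.

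The cost is a short listing exercise, with no extra students, staff or measurements. The downside is a narrower frame and a slightly less representative pair; with several criteria plus distance, few pairs may qualify.

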### Participant recruitment and data collection

The study will follow a fixed study design (Additional file 1). Sample size is determined based on a previous study where a mean difference of BMI was found 1.48 between intervention and non-intervention adolescent groups after 3-months of motivational interview [23]. Expecting a similar difference, calculated sample size is 274 in each group considering effect size (E) = 1.48; standard deviation (S) = 5.98; standardized effect size (E/S) = .25; significance level, α (two-sided) = 0.05; β = 1- power = 0.2, non-response rate = 5%]. A complete list of grade-ten students will be prepared after collecting their class roll and batch number from the administrative offices of the selected schools. All the students of grade-ten will be invited to participate in the study through announcement and personal contact prior to the date of data collection.

At first, a baseline survey will be conducted among the grade ten students of both schools by a pre-tested questionnaire to attain their current status of knowledge, attitude and practices related to NCDs. Then, students from the intervention school who reported at least two NCDs risk behaviors will be invited to participate in a health education session through phone call to their parents. Selected students who will present at the day of intervention will be considered having implied consent from their parents and will be enrolled in the intervention group up to the attainment of the required sample size. Enrolled students will be given intervention through health education session. Students with any kind of physical disability or limited movement will be excluded from the study. Students from the control group will receive a one-hour session on carrier guidance. Students will be kept blind about the intervention they received. After 3 months of the baseline survey, a post-intervention survey will be conducted among the participants from both intervention and control group using the same questionnaire.

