### Statistical analysis plan

Descriptive analysis: Socio-demographic data of the participants e.g. gender, parental occupation, parental education status, family history of NCDs, family living standard will be obtained for both intervention and control school. All categorical variables will be summarized in frequency and percentages and continuous variables in mean and standard deviation. To estimate the association of these characteristics of intervention and control group, t-tests and chi-square tests will be done.

Inferential analysis: To estimate the efficacy of the intervention, before-after data will be analyzed and paired t-test and McNemar’s chi-square tests will be done in this regard. Also, comparison will be done between the intervention and control group for pre and post-intervention status of knowledge, attitude and practices.

Association analysis: Binary regression analysis will be done to estimate the association between socio-demographic variables with changes in the outcome variables- knowledge, attitude, and practice for both groups. Also, to estimate the association of knowledge score and attitude with the change in self-reported practices, regression analysis will be done.

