Issue 5: NCDsUnderstanding the basic pathology and aetiology of NCDs with special emphasis on atherosclerosis, stroke, heart disease, diabetes and hypertensionUnderstanding and identifying the effect of lifestyle behavior on NCDsRecognizing the preventive ways of NCDsRaising curiosity on how can and to what extent should one apply the preventive ways to avert NCDs

Issue 6: Preventive waysUnderstanding the daily requirements of different foods to prevent NCDsEnabling to make one’s own platterUnderstanding the recommended physical activity requirements at adolescent ageEnabling to perform aerobic and stretching exerciseUnderstanding the ways to maintain normal body weightMaking healthy choices for lifestyle behavior and setting goals

The intervention will be delivered through a health promotion session using multi-media projector, flip paper and pen and leaflets. Each session will be of 2 h duration. A sequential framework of the intervention conceptualizing from a standard MI training manual [29] and SCT theory [18] will be used to train the facilitators.

Here is the sequential framework of the intervention workout:

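### The 80% power is for a between-group BMI difference that the analysis section never names, so power for the knowledge, attitude and practice analyses is unsupported

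*Protocol article*

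**What the plan says.** Under *General objective*, the protocol article sets out to "investigate the efficacy of a health education intervention to reduce NCD related behavioral risk factors among adolescents in institutional settings".

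Under *Participant recruitment and data collection*, the basis for the size of the study is given as: "Sample size is determined based on a previous study where a mean difference of BMI was found 1.48". In full, the effect is a "mean difference of BMI was found 1.48 between intervention and non-intervention adolescent groups after 3-months of motivational interview", with "standard deviation (S) = 5.98" and "standardized effect size (E/S) = .25". Significance is 5% two-sided, power 80% and non-response 5%, giving 274 per group.

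Under *Statistical analysis plan*, efficacy is estimated from before-after data with paired t-tests and McNemar tests. For the two schools, "comparison will be done between the intervention and control group for pre and post-intervention status of knowledge, attitude and practices". The regressions concern the same three domains. BMI does not appear in that section.

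Under *Outcome variables* and the headings that follow, the article lists knowledge, attitude, several practices, blood pressure, BMI and circumferences. None is singled out as primary.

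Under *The intervention*: "The intervention will be delivered through a health promotion session using multi-media projector", each session lasting 2 hours. Follow-up is fixed from baseline: "After 3 months of the baseline survey, a post-intervention survey will be conducted".

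**The concern.** A power statement belongs to one outcome, one contrast and one assumed effect. Here all three differ from what the analysis section describes. The outcome is BMI, while the objective and the between-group analysis concern behaviour. The contrast is between groups, while the efficacy tests are within group. The effect comes from a study of motivational interview. This study gives a group session that draws on some principles of that method, to students who qualify by reporting at least two risk behaviours and not by weight. The BMI classes include underweight.

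The sample size is the only place where any outcome receives priority, and the outcome it favours is one that the between-group comparison leaves out. A reader will take the 80% as backing for a conclusion about behaviour, and no stated input gives it that role.

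**Working it through.** **Inputs.** E = 1.48, S = 5.98, E/S = 0.25, α = 0.05 two-sided, power 80%, non-response 5% and N = 274 per group, all from *Participant recruitment and data collection*. Normal quantiles: 1.960 and 0.842, sum 2.802.

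**1. The plan's own figure.** For two independent means, n = 2 × (2.802)² / d².
- d = 1.48/5.98 = 0.2475: n = 256.3, rounded up to 257; 257/0.95 = 270.5, so 271.
- d = 0.25: n = 251.2, rounded up to 252; 252/0.95 = 265.3, so 266.
- The shortcut 16/d² = 261.2, times 1.05, gives 274.3, which may be how 274 arose.

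Both standard results lie within 3% of 274, and the plan's figure is slightly conservative. It is a two-sample comparison of means, not a paired or McNemar calculation.

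**2. Power for the stated contrast.** 274 × 0.95 = 260 evaluable per group. The standard error in SD units is √(2/260) = 0.0877. Then 0.2475/0.0877 − 1.960 = 0.862, which gives 80.6% power.

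**3. Match to the named analyses.**

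| | Sample size | Analysis section |
|---|---|---|
| Outcome | BMI | Knowledge, attitude, practices (between groups); variables not listed (within group) |
| Contrast | Between groups | Within group for efficacy; between groups for the three domains |
| Effect and SD | 1.48 and 5.98 | None given |

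No row ties the 80% to a test that the section names.

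**4. What 260 per group can detect at 80% power, treating students as independent.**
- Score, between groups: 2.802 × 0.0877 = 0.246 SD.
- Binary practice, between groups: the smallest Δ = p₁ − p₂ satisfying Δ ≥ 1.960 × √(2p̄(1−p̄)/260) + 0.842 × √((p₁q₁ + p₂q₂)/260). From 50%, try Δ = 0.122 (p₂ = 0.378, p̄ = 0.439): the right side is 0.0853 + 0.0364 = 0.1217, so about 12 points suffice. The same search gives 6.3 points from 10%, 10.6 from 30%, 11.8 from 70% and 8.6 from 90%.
- Change within one arm: 2.802/√260 = 0.174 SD of the change.

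**5. Dependence on 1.48.** The text gives no basis for a smaller effect, so this range is an assumption. At 75%, 50% and 25% of 1.48, power at 260 per group is 56%, 29% and 10%.

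**6. Clustering.** Each group is one school. The article gives no intraclass correlation, so 0.01 to 0.05 is assumed. The design effect 1 + 259 × ICC runs from 3.59 to 13.95. The detectable 0.246 SD becomes 0.246 × √3.59 = 0.47 to 0.246 × √13.95 = 0.92. The figures in step 4 are therefore optimistic.

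**The case against.** The strongest reply has three parts, and much of it stands.

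First, the sample size itself is sound. 274 is slightly above what the inputs require and gives 80% power for any continuous between-group outcome with a standardised difference of about 0.25. A paired test of a 0.2475 SD change would have 92% power at an assumed correlation of 0.3 and 98% at 0.5. A reader might infer that no planned outcome reaches 80% power. The documents do not support that: they give no effect or SD for knowledge, attitude or practice, so power there is unknown and could be higher or lower.

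Second, BMI is a listed outcome. Obesity is one of the intervention's topics, and the paired t-test sentence does not restrict its variables, so BMI may well be tested before and after. What is absent is a between-group BMI test, which is the contrast the sample size assumes. A list of tests per outcome can be left to a fuller plan. But this article prints both a power basis and an analysis section, and the two do not match.

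Third, a reader might infer that 1.48 came from a 3-month programme. The wording can equally mean a 3-month follow-up, and the source is not at hand. A single session is likewise the likely but not the only reading, since the same section also uses the plural. The transfer is unexplained either way, because the article itself says its intervention uses only some principles of motivational interview.

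**Conclusion.** The point holds as a mismatch between the power basis and the analysis. It is not an arithmetic error and not a demonstrated shortfall of power. The 80% applies to a between-group BMI difference of 1.48 with SD 5.98; the analysis section names no such comparison, and the behavioural objective has no stated power. At the planned size, ignoring clustering, the study could detect about 0.25 SD on a score or about 12 points from 50% on a practice. With one school per arm the true figures are worse by an amount the article cannot supply.

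Two further inferences are tempting and should not be drawn. A numerical family-wise error rate would need a count of tests and their correlation, and the article gives neither. A claim that follow-up after the session is too short would need the interval from baseline to session, which is also not given; the article consistently dates the endline from baseline.

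**What to change.** Keep 274 per group and change three things.

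1. **Primary outcome.** Name one practice outcome from those already defined under *Practice*, analysed as the baseline-adjusted difference between groups at endline. Make the remaining outcomes secondary or exploratory, BMI included.
2. **Selection.** Apply the criterion of at least two risk behaviours to the baseline data of both schools. The article states it only for the intervention school. Selecting one arm on a high baseline would produce regression to the mean in the intervention's favour. For the same reason, a count of risk behaviours should not become the primary outcome unless this is done.
3. **Power sentence.** Replace the BMI basis with, for example: With about 260 evaluable students per group, the study has 80% power to detect a between-group difference of about 0.25 SD on a score, or about 12 percentage points from 50% on a binary practice. These figures ignore clustering by school, with one school per arm, and are therefore optimistic.

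**Cost.** Mostly rewording, with no increase in the target number. The power statement becomes less favourable and BMI loses its implied priority. The control school must now supply 274 students who meet the criterion. The article does not give the grade-ten rolls, so this has to be checked; if fewer qualify, the detectable differences should be recomputed.
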